## Abstract

**Background:**

Depression frequently first emerges during adolescence, and one in five young people will experience an episode of depression by the age of 18 years. Despite advances in treatment, there has been limited progress in addressing the burden at a population level. Accordingly, there has been growing interest in prevention approaches as an additional pathway to address depression. Depression can be prevented using evidence-based psychological programmes. However, barriers to implementing and accessing these programmes remain, typically reflecting a requirement for delivery by clinical experts and high associated delivery costs. Digital technologies, specifically smartphones, are now considered a key strategy to overcome the barriers inhibiting access to mental health programmes. The Future Proofing Study is a large-scale school-based trial investigating whether cognitive behaviour therapies (CBT) delivered by smartphone application can prevent depression.

**Methods:**

A randomised controlled trial targeting up to 10,000 Year 8 Australian secondary school students will be conducted. In Stage I, schools will be randomised at the cluster level either to receive the CBT intervention app (SPARX) or to a non-active control group comparator. The primary outcome will be symptoms of depression, and secondary outcomes include psychological distress, anxiety and insomnia. At the 12-month follow-up, participants in the intervention arm with elevated depressive symptoms will participate in an individual-level randomised controlled trial (Stage II) and be randomised to receive a second CBT app which targets sleep difficulties (Sleep Ninja) or a control condition. Assessments will occur post intervention (both trial stages) and at 6, 12, 24, 36, 48 and 60 months post baseline. Primary analyses will use an intention-to-treat approach and compare changes in symptoms from baseline to follow-up relative to the control group using mixed-effect models.

**Discussion:**

This is the first trial testing the effectiveness of smartphone apps delivered to school students to prevent depression at scale. Results from this trial will provide much-needed insight into the feasibility of this approach. They stand to inform policy and commission decisions concerning if and how such programmes should be deployed in school-based settings in Australia and beyond.

**Trial registration:**

Australian and New Zealand Clinical Trial Registry, ACTRN12619000855123. Registered on 31 May 2019.

Clinical Trial Notification Scheme (CTN), CT-2019-CTN-02110-1-v1. Registered on 30 June 2019.

## Background

According to the World Health Organization, depression is the leading cause of disability worldwide [1]. For many individuals, depression first emerges during adolescence [2], between age 10 and 24 years [3]. Approximately one in five young people will experience a depressive episode by the age of 18 years [4], with earlier onset being associated with a range of adverse consequences including poor academic performance, low levels of school attendance, social dysfunction, substance abuse, anxiety, suicidality, poor sleep, diabetes and metabolic syndrome [5–7]. As adolescents develop, the foundations are laid for successful transition into the varied roles of adulthood including the time in life when employment productivity peaks. Experiencing depression as a young person can negatively impact psychological, social, emotional, educational and vocational pathways into adulthood, with profound implications for the individual, their families and their communities, as well as the economy [5, 8]. The global cost of mental illness is nearly US$2.5 trillion, two-thirds of which is incurred via indirect costs such as unemployment. This cost is expected to increase to US$6000,000,000,000 by 2030 [9, 10]. By way of benchmarking, total global health expenditure in 2009 was US$5.1 trillion, of which less than 2% is spent on mental health [11]. The immense cost of mental illness, together with the social and emotional consequences associated with earlier onset, highlights the crucial importance of prevention or intervention early in the course of illness, and, consequently, at an early age.

There has been little progress in recent years addressing this challenge. Estimates suggest that only 13% of the disease burden due to depression can be alleviated through current treatments and service models [12]. Even with optimal clinician competence, improved access and treatment adherence, only 36% of the burden is avoidable, leaving substantial unaddressed morbidity and disability [12]. Currently, fewer than one-third of young people seek help and gain access to first-line interventions for reasons that include accessibility, stigma and affordability [13]. Of those who seek professional help, between 30 and 50% of young people do not respond to treatment [14], and among those who do, over 45% will experience a subsequent depressive episode [15]. This has led to growing recognition that treatment alone will not successfully reduce the burden of depression at a population level [16].

Prevention represents a separate pathway through which the burden of depression may be addressed. There has been bourgeoning interest in the use of preventive approaches, with several high-quality but small-scale prevention studies demonstrating that the prevention of depression is possible in school-aged young people. Several recent meta-analyses have examined the effect of psychological prevention programmes specifically on adolescents and found consistent but small effect sizes in favour of delivering CBT for depression, at least in the short term [17–19]. Of the prevention programmes that are available, those based on cognitive behaviour therapy (CBT) have been the most frequently evaluated interventions, with evidence to support these approaches [20]. Other approaches may prove effective but have not yet been subject to rigorous empirical evaluation. CBT involves challenging unhelpful thoughts or beliefs, by gathering evidence which contradict these thoughts or beliefs from real-world situations. This leads to changes in emotion and behaviour. CBT is structured, brief and time-limited, and aims to help individuals develop skills and strategies to manage their own mood and depression. Prevention approaches can be delivered either universally to all individuals within an identified population regardless of risk (universal prevention), or targeted to those with risk factors such as low socio-economic background (selective prevention) or to those who have sub-threshold disorder symptoms (indicated prevention). While there is evidence for all three prevention approaches [18, 19, 21], there have typically been larger effects reported for targeted approaches, at least in part due to limitations in the statistical power of universal prevention studies [22].

Despite consistent statistically and clinically meaningful effects in existing prevention studies, these studies have been limited by several factors. First, trials have generally involved small sample sizes, and the consequent limited statistical power means that potential effects go undetected and/or are measured imprecisely. Specifically, the median sample size identified in a recent meta-analysis of 47 studies examining the prevention of depression was 208, with an average effect size of *g* = 0.23 [19]. Samples of this size are insufficient because preventive programmes, particularly universally delivered programmes, necessarily expose a large proportion of individuals not at risk to the intervention, and yield small to modest effects because of the low base rates of disorder in general population samples [21]. Second, studies have rarely involved follow-up beyond 12 months, which limits what is known about long-term preventive effects. Third, studies have relied solely on self-report or clinician-reported symptoms. While subjective reports reflect the gold-standard approach and are useful clinically, there is much to be gained by the inclusion of additional objectively quantifiable data sources (e.g., health care utilisation data, smartphone-collected sensor data). Fourth, most prevention approaches involve the delivery of a single intervention or programme. There is rarely an option to identify who is most likely to respond to different interventions, or for a tiered approach whereby individuals for whom one approach has not been effective may try a different approach afterwards. This is potentially a missed opportunity given that not everyone will respond to a single, or the first-line, approach. Finally, CBT has, until recently, been delivered to young people generally over 6–12 sessions using face-to-face approaches which are challenging to scale due to the expertise and cost required to deliver such programmes. Digital approaches may be easier to scale up; however, in a review of 146 randomised controlled prevention trials, only two involved digitally delivered interventions [18]. In light of these limitations, there is scope to improve on and extend the empirical base to understand the effects of depression prevention programmes.

### The current study

The Future Proofing Study has been designed to overcome these challenges by conducting a large school-based randomised controlled trial (RCT) testing whether depression can be prevented using a CBT programme delivered by smartphone application. Research evidence to date suggests that digital CBT programmes for depression delivered in schools can be effective in reducing and preventing depression [23]. Partnering in the delivery of prevention programmes is a natural fit for schools, which are increasingly seen as settings in which to foster emotional skill development alongside traditional academic learning. Mental ill health is associated with poorer academic performance [24], and depressed young people miss an average of 22 days of school per year [6], making mental well-being in line with the goals of educators and school administrators. Importantly, schools provide access to large student samples which are more representative of the general population than other settings, such as mental health services or medical practices. In addition, the potential to deliver a prevention programme to all students universally may help reduce the stigma often associated with the delivery of mental health interventions only to those with symptoms [13].

This trial will involve up to 10,000 Australian school students who will be followed up for 5 years. A sample of this size provides appropriate statistical power to definitively and precisely evaluate effectiveness, as well as providing the opportunity to conduct robust moderation and mediation analyses. All study protocols will be delivered to participants digitally. The intervention/s will be delivered by smartphone application (apps) and study surveys can be completed on any Internet-enabled device (smartphone, tablet, laptop). This delivery method overcomes the aforementioned challenges associated with delivery by trained health professionals or teachers. It is simply too costly to train enough of the workforce to deliver CBT prevention programmes either individually or in small groups to make an impact at a population level. Delivering interventions digitally is more cost-effective than face-to-face therapies [25]. Moreover, programmes using a smartphone app for delivery do not compromise effectiveness [26]. Testing smartphone apps represents a major innovation of this project, with most evaluation of digital programmes focusing on Internet-based approaches [27]. Digital technologies, and specifically smartphones, are now considered a key strategy to overcome the barriers inhibiting access to mental health programmes. This mode of delivery is appropriate given that young people show a preference for digital technologies when given the choice, due to the anonymity, convenience and privacy [12, 28].

This SPIRIT-compliant protocol describes the methodology for a multi-stage, two-arm, parallel group RCT (Additional file 1). At Stage I, a cluster RCT will be undertaken to evaluate the effectiveness of SPARX, which is an app-based CBT gaming intervention [29]. This intervention has been tested in the Australian adolescent population and was found to be effective for the prevention of depression [23]. In the current trial, SPARX will be delivered to Year 8 students (who are typically aged 12–14 years). The control group will consist of Year 8 students of an equivalent demographic who will not receive any intervention. Participants across both arms will be followed longitudinally over 5 years. The choice to use a non-active (treatment-as-usual) comparator was made to avoid placing unnecessary burden on the participants and schools, which would have been required to provide an attention-matched placebo intervention—an intervention that would have required an equivalent level of effort to that of the active condition—that would most likely provide no benefit. Other candidate programmes that may have benefited other outcomes such as lifestyle or nutrition programmes could not serve as a fair control condition because of their likely impact on mental health. At Stage II (12 months following baseline), an individual-level RCT will be conducted within the intervention arm. Individuals who show elevated symptoms of depression at 12 months will be randomised to an intervention condition that receives a second CBT app which targets sleep difficulties (Sleep Ninja) or a control condition. Sleep Ninja focuses on sleep disturbances and delivers cognitive behaviour therapy for insomnia (CBT-I). An intervention targeting sleep difficulties was selected because sleep disturbance is both a risk factor and a symptom of depression, with efficacy supporting its use in the prevention and treatment of depression in both adults and adolescents [28, 30–32].

### Aims

This trial will investigate the impact of two mental health apps on adolescent depression. The first objective of this trial is to determine whether delivering a CBT programme via smartphone application can prevent high school students in Year 8 from developing depressive symptoms compared to students in the control arm. This study will assess the effect of the programme on a range of secondary outcomes, which include mental health symptoms (distress, anxiety, insomnia) at post intervention, 6, 12, 24, 36, 48 and 60 months. The effect of a second intervention on depression in those who show elevated depressive symptoms 1 year after using the first SPARX app will also be evaluated. Individual differences associated with response to the interventions will also be investigated, including demographics, history of mental illness, personality factors, social support, social media use and gender identification, among a range of other variables (see Table 1). In the control group, these factors will be examined as possible predictors for the development of depressive symptoms and other mental health problems.

**Table 1 Tab1:** Summary of primary, secondary and tertiary outcome measures, potential mediating and risk factors, and data collection time points

Outcome measure		Baseline	Post (Stage I)	6 months	12months	Post (Stage II)^a^	24 months	36 months	48 months	60 months
Primary outcome measure										
Depression	Patient Health Questionnaire: Adolescent Version (PHQ-A)	✓	✓	✓	✓	✓	✓	✓	✓	✓
Secondary outcome measures										
Psychological distress	Distress Questionnaire 5 (DQ5)	✓	✓	–	✓	–	✓	✓	✓	✓
Anxiety	Spence Children’s Anxiety Scale (SCAS) including Generalized Anxiety and Social Phobia subscales	✓	✓	–	✓	✓	✓	✓	✓	✓
Insomnia	Insomnia Severity Index (ISI)	✓	✓	–	✓	✓	✓	✓	✓	✓
Tertiary outcome measures, potential mediating variable risk factors										
Suicidal ideation	Suicidal Ideation Attributes Scale (SIDAS)	✓	✓	–	✓	–	✓	✓	✓	✓
Suicide behaviour	Youth Risk Behaviour Survey (YRBS)	✓	✓	–	✓	–	✓	✓	✓	✓
Externalising behaviours	Strength and Difficulties Questionnaire (SDQ)	✓	✓	–	✓	–	✓	✓	✓	✓
Eating disorders	Screen for Disordered Eating (SDE)	✓	✓	–	✓	–	✓	✓	✓	✓
Self-harm	Single question from Self-Harm Questionnaire	✓	✓	–	✓	–	✓	✓	✓	✓
Alcohol use	Questions from previous National Drug and Alcohol Research Centre, UNSW studies	✓	✓	–	✓	–	✓	✓	✓	✓
Other substance use	Questions from Australian Institute of Health and Welfare 2007 National Drug Strategy Household Survey	✓	✓	–	✓	–	✓	✓	✓	✓
Psychosis	Adolescent Psychotic-like Symptom Screener (APSS)	✓	✓	–	✓	–	✓	✓	✓	✓
Sleep quality	Pittsburgh Sleep Quality Index (PSQI)	✓	✓	–	✓	✓	✓	✓	✓	✓
Quality of life	Child Health Utility 9D (CHU-9D)	✓	✓	–	✓	–	✓	✓	✓	✓
Well-being	Short-form Warwick–Edinburgh Mental Well-Being Scale (SWEMWBS)	✓	✓	–	✓	–	✓	✓	✓	✓
Demographics	Age, ethnicity, location, language, perceived socio-economic status	✓	–	–	–	–	–	–	–	–
Height and weight	Height (cm), weight (kg)	✓	–	–	✓	–	✓	✓	✓	✓
Personality	Big Five Inventory-10 (BFI-10)	✓	–	–	–	–	–	–	–	–
School connectedness	Items from OECD Programme for International Student Assessment (PISA)	✓	✓	–	✓	–	✓	✓	✓	–
Social support	Schuster Social Support Scale (SSSS)	✓	✓	–	✓	–	✓	✓	✓	✓
Social media use	Maladaptive Facebook Use Survey (MFUS), adapted to apply to social media use more broadly	✓	✓	–	✓	–	✓	✓	✓	✓
Gender identification	Sex at birth and current gender identification	✓	–	–	✓	–	✓	✓	✓	✓
Sexual identification and preferences	Single item for each	✓	–	–	✓	–	✓	✓	✓	✓
Sexual behaviour	History of sexual behaviour	–	–	–	–	–	✓		✓	
Romantic relationships	History of romantic relationships	✓			✓		✓	✓	✓	✓
Trauma	Adapted Behavioural Risk Factor Surveillance System—Adverse Childhood Experience (BRFSS-ACE)	✓ no abuse items	–	–	–	–	–	–	✓	–
History of diagnosed mental health condition	Diagnosed mental health conditions	✓	✓	–	✓	–	–	–	✓	✓
Hospitalisation	History of hospitalisation	✓	✓	–	✓	–	–	–	✓	✓
History of diagnosed disability	Diagnosed disability	✓	–	–	–	–	–	–	✓	–
Pubertal development	Menarche, voice-breaking and Tanner stages	✓	–	–	✓	–	✓	✓	✓	✓
Bullying	From previous school trials	✓	✓	–	✓	–	✓	✓	✓	✓
App feedback/acceptability										
App feedback	Future Proofing App Feedback Survey	–	✓	–	–	–	–	–	–	–
App feedback	Post-intervention SPARX-FP Feedback Survey	–	✓	–	–	–	–	–	–	–

*UNSW* University of New South Wales

^a^Participants selected to take part in Stage II of the trial only

The second objective of the trial is to identify the predictors of mental health outcomes from digital behavioural and cognitive data collected using participants’ smartphones (see Table 2 for details). Sensor data will be collected from smartphones to provide information about activity levels (accelerometery), movement through space (GPS) and voice patterns to generate a ‘digital phenotype’ for each participant [33–35]. Digital phenotyping can be understood as using sensor data collected by personal devices to quantify the individual-level human phenotype. One of the functions of profiling individuals using digital phenotypes in this way is to make predictions about changes in mental health. The sensors in smartphones provide a non-intrusive, minimally burdensome and scalable method to investigate the effect of activity and behaviour on mental health. Evidence of the validity of this approach is beginning to emerge, with location variability now showing an association with depression outcomes in small studies of adults [36, 37]. However, the use of digital phenotyping approaches in young people at scale has not yet been undertaken. For participants in the intervention group, this information will be combined with intervention usage data and other study measures to explore predictors of response and non-response to the intervention apps. In the control group, this information will be used to prospectively examine predictors of psychopathology.

**Table 2 Tab2:** Future Proofing app tasks, data and collection time points

Smartphone-collected data	Approximate time	Baseline	Week 1	Week 2	Week 3	Week 4	Week 5	Week 6	6 months	12 months	24 months	36 months	48 months	60 months
Self-rated mood visual analogue scale (VAS)	1 min	•	•	•	•	•	•	•	•	•	•	•	•	•
Affective card sorting task (CST) cognitive game	3 min	•	•	•	•	•	•	•	•	•	•	•	•	•
Affective backward span task (BST) cognitive game	3 min	•	•	•	•	•	•	•	•	•	•	•	•	•
Speed of typing task	2 min	•	•	•	•	•	•	•	•	•	•	•	•	•
Voice sample task	2 min	•		•		•		•	•	•	•	•	•	•
Accelerometery (movement) device sensor data	3 months of continuous data collection													
Gyroscope (movement) device sensor data	3 months of continuous data collection													
GPS (location) device sensor data	3 months of continuous data collection													

The third objective of this trial is to evaluate the implementation of the proposed CBT-based depression prevention programme in the school environment. The data that will be collected to meet this objective will combine intervention usage with qualitative and quantitative methods. A protocol for the process evaluation of the programme implementation will be detailed elsewhere.

Three different forms of data will be collected from this trial to address each of the objectives: self-report questionnaires (first objective), smartphone-recorded sensor data and ecological momentary assessment data (second objective), and usage and implementation data (third objective). This study will also utilise health and education datasets as a fourth form of data that will be linked to the main study datasets 1 year after the trial commences, and then periodically until the trial is complete. Linked data will include academic outcomes, health service utilisation and infant development, alongside births and deaths records. Linkage will allow for a more complete picture of the education outcomes and the health of the sample and a cost-effectiveness analysis.

The first form of data (self-report questionnaire data) will be reported in the primary outcome paper and limited to primary and secondary outcomes. All other data types will be reported and published separately.

### Hypotheses

The primary hypothesis is that participants allocated to the intervention arm will show a smaller increase in depressive symptoms relative to those in the control group at 12 months, measured using the self-report Patient Health Questionnaire—Adolescent Version (PHQ-A) [38]. Secondary hypotheses are that depressive symptoms will be lower (e.g., show a smaller increase) in the intervention arm relative to the control arm at other assessment points (post intervention, 6, 24, 36, 48 and 60 months). Using the pre-defined clinical cut-off points on the PHQ-A will also allow a comparison between likely cases of depression across the two arms. It is hypothesised that the percentage of depression cases will be lower in the intervention arm relative to the control arm at post intervention, 6, 12, 24, 36, 48 and 60 months. Secondary mental health outcomes are psychological distress, anxiety and insomnia, and are expected to be lower in the intervention arm relative to the control, at post intervention, 12, 24, 36, 48 and 60 months. Additional outcomes including suicidality, substance use and sleep quality will be reported separately.

For participants in the intervention condition who show clinically significant depressive symptoms at 12 months (PHQ-A score > 10) and who enter Stage II of the trial, it is hypothesised that those who receive the Sleep Ninja intervention will report greater decreases in symptoms of depression (primary outcome), anxiety and insomnia (secondary outcomes) from pre to post intervention (Stage II) and from 12 to 24 months (after they receive the Sleep Ninja intervention), relative to the Stage II control arm.

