### Primary outcome measure

#### Patient Health Questionnaire—Adolescent Version

The primary outcome measure is depression severity measured at 12 months post baseline using the Patient Health Questionnaire for Adolescents (PHQ-A) [38]. PHQ-A depression scores will also be collected at baseline, 6 weeks post intervention (Stages I and II) and at 6, 24, 36, 48 and 60 months post baseline. The PHQ-A is a validated modification of the PHQ-9 for adolescents, a nine-item self-administered depression severity screening and diagnostic tool based on DSM-IV criteria. The scale assesses the frequency of occurrence of nine depression symptom criteria during the previous 2 weeks, with items rated on a 4-point scale ranging from 0 (‘Not at all’) to 3 (‘Nearly every day’). Total scale scores on the PHQ-A depression scale can range from 0 to 27, with higher scores reflecting more severe depressive symptoms. The accepted clinical cut-off points are as follows: a score of 0–4 indicates nil to minimal symptoms, 5–9 indicates mild symptoms, 10–14 indicates moderate symptoms, 15–19 indicates moderately severe symptoms and 20–27 indicates severe symptoms. The psychometric quality of the PHQ-9 and PHQ-A is well established [38, 40].

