### Sample size

Separate sample size estimates were derived to determine the numbers of participants needed to meet the aims of each trial stage. Power was set at 0.80, α = 0.05 (two-tailed), and a correlation of 0.5 assumed between baseline and endpoint symptom scores. To account for possible clustering effects at Stage I (i.e., participants from the same school having prognostically relevant characteristics and outcomes more alike than between schools), a design effect [84] was calculated assuming an intraclass correlation coefficient (ICC) of 0.03 (based on previous school-based studies) [85] and a cluster size of 50 students, yielding a design effect of 2.47. In order to detect a mean standardized difference of 0.3 between conditions at Stage I, a sample of 870 participants would be needed (435 per arm). Allowing for up to 30% attrition, recruitment of 1244 participants would be required (622 per arm).

Using similar parameters for Stage II (without a design effect) would require recruitment of 368 participants in total to detect the same effect size. However, participants in this stage must meet eligibility requirements regarding elevated symptoms and failure to respond to the first-stage intervention. They must also be willing to participate. Accordingly, a scenario involving recruitment of 10,000 participants at Stage I was considered, assuming 7000 participants would have endpoint data available at 12 months (allowing for 30% attrition). Conservatively estimating 20% having PHQ-A scores ≥ 10, 25% showing a reduction due to the Stage I intervention and that 50% of those eligible to enrol at Stage II do so, 525 participants would enter this stage II, with endpoint data available for at least 368 (allowing for up to 30% attrition). This sample would enable the detection of differences in changes in symptomatology scores of comparable size to those in Stage I of the trial (*d* = 0.29).

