### Randomisation

For Stage I, cluster randomisation (at the school level) will be employed for administrative convenience, to avoid control condition contamination, and for the ecological validity of providing the intervention at the cluster level. Schools will be randomised after they are recruited into the trial. The trial statistician who is not involved in the day-to-day running of the trial will perform the randomisation, and the identity of the school will be concealed from the statistician.

Schools will be randomised with a 1:1 allocation, as per a computer-generated randomisation schedule. Balance between the trial arms will be achieved by stratifying based on school size, school location (metropolitan vs. regional), school type (co-educational or gender selective) and Index of Community Socio-Educational Advantage (ICSEA) level. For Stage II, individual-level randomisation with a 1:1 allocation using a computer-generated randomisation schedule stratified by gender and depression severity scores will be employed. This procedure is automated through the Black Dog Institute research platform. Permuted block randomisation will be used at both stages but will not be disclosed to ensure concealment. Allocation to arms is not directly communicated to schools. However, because the study has no control intervention, schools, participants and study operational staff will be aware of school allocation to the intervention arm. With the exception of the trial data manager, other individuals not involved in the day-to-day running of the trial will remain blind to allocation. All outcome assessments are conducted electronically and not subject to assessor bias. Unblinding at the conclusion of analysis will be performed by the trial data manager with authorisation from the Trial Steering Committee.

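### Stage II entry is PHQ-A above 10 in the Hypotheses but PHQ-A of 10 or more in the Sample size, so a student scoring exactly 10 is excluded in one place and counted in the other

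*Protocol article*

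**What the plan says.** The Hypotheses section sets out the Stage II hypothesis for intervention-arm students "who show clinically significant depressive symptoms at 12 months (PHQ-A score > 10") and who go on to Stage II. One paragraph earlier, the same section relies on the instrument's established thresholds to define cases: "Using the pre-defined clinical cut-off points on the PHQ-A will also allow a comparison".

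The Sample size section turns Stage I recruitment into a Stage II sample. It starts from 10,000 recruits, "assuming 7000 participants would have endpoint data available at 12 months", and continues "Conservatively estimating 20% having PHQ-A scores ≥ 10". It then allows 25% to improve because of the first app and 50% of eligible students to enrol. The result is that "525 participants would enter this stage II, with endpoint data available for at least 368", with a detectable difference of d = 0.29.

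The description of the PHQ-A gives a total of nine items scored 0 to 3 (range 0–27) and lists the accepted bands, among them "10–14 indicates moderate symptoms".

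The Abstract, The current study, Aims, Interventions and Discussion refer to Stage II entrants only as having elevated symptoms or symptoms, with no number.

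**The concern.** The PHQ-A total is an integer, so a score of exactly 10 can occur. Under the Hypotheses that student is outside Stage II. Under the Sample size the same student is part of the pool from which entrants are drawn. One threshold therefore has two values in current text.

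The threshold decides which adolescents are individually randomised to the second app. If the stricter version is applied, the 20% prevalence is stated for the wrong group, and the yield and detectable effect derived from it are too favourable. If the looser version is applied, students scoring 10 are randomised but fall outside the population named in the hypothesis. The Randomisation section says of Stage II allocation that "This procedure is automated through the Black Dog Institute research platform". An automated process needs one unambiguous definition of who is passed to it.

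**Working it through.** **Inputs, all from the Sample size section unless noted**

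- 12-month data available: 7000
- PHQ-A of 10 or more: 20%
- Improved because of the first app: 25%, so 75% remain
- Uptake among those eligible: 50%
- Stage II attrition: 30%, so 70% have endpoint data
- Power 0.80, two-sided α = 0.05, correlation 0.5
- Allocation 1:1 at each stage (Trial design)
- Stage II population: intervention arm only (The current study, Hypotheses)

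**Step 1. Reproduce the protocol's figures.**

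Entrants: 7000 × 0.20 × 0.75 × 0.50 = 525. With endpoint data: 525 × 0.70 = 367.5, i.e. 368.

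With correlation 0.5, the SD of a change score is √(2 × (1 − 0.5)) = 1 in raw SD units. The detectable effect for N in total, split equally, is

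d = (1.960 + 0.842) × √(4/N) = 2 × 2.802 / √N.

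For N = 368 this is 0.292, which matches the stated 0.29. Adjusting for baseline instead (variance factor 1 − 0.5² = 0.75) gives 0.253, which does not match. The protocol's figure is therefore a change-score calculation resting on the 20% stated for ≥ 10.

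**Step 2. Apply the stricter rule to the same chain.**

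Let s be the share of students at 10 or more who score exactly 10. The document does not give s; a range of 5–20% is assumed. Entrants and endpoint numbers are multiplied by (1 − s).

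| s | Entrants | With endpoint data | Detectable d | Power at d = 0.29 |
|---|---|---|---|---|
| 0 (rule ≥ 10) | 525 | 367.5 | 0.292 | 79% |
| 5% | 498.8 | 349.1 | 0.300 | 77% |
| 10% | 472.5 | 330.8 | 0.308 | 75% |
| 20% | 420 | 294 | 0.327 | 70% |

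**Step 3. Check the base of the chain.**

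The only factor of 0.50 in the chain is uptake, so no step restricts the 7000 to one arm. Yet The current study says that "an individual-level RCT will be conducted within the intervention arm". Assuming that 1:1 allocation of schools gives about half the students, the base is 3500:

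3500 × 0.20 × 0.75 × 0.50 = 262.5 entrants; × 0.70 = 183.75 with endpoint data; d = 5.604 / √183.75 = 0.413.

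| s | Entrants | With endpoint data | Detectable d |
|---|---|---|---|
| 0 (rule ≥ 10) | 262.5 | 183.8 | 0.413 |
| 5% | 249.4 | 174.6 | 0.424 |
| 10% | 236.3 | 165.4 | 0.436 |
| 20% | 210 | 147 | 0.462 |

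Most of the gap between 0.29 and these values comes from the base. The cut-off adds 0.01 to 0.05.

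**The case against.** The contradiction itself cannot be disputed; its weight can. There are five points on the other side.

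- **The intended rule can be inferred.** The moderate band starts at 10. The fallback in the Sample size section, which would top up Stage II from the highest-scoring 20% of the population, matches the 20% assumed at 10 or more. This stands as evidence that ≥ 10 was meant. It does not change what the Hypotheses say.
- **Neither place is an eligibility section.** One is a hypothesis and the other a planning prevalence, and the article condenses a full protocol that may hold a single rule. That would answer a complaint about missing detail. Here the published text gives two incompatible values, and the Hypotheses are the only place that attaches a number to those who enter.
- **The automation sentence concerns allocation, not screening.** This is fair. Nothing suggests that the platform was set up wrongly; the sentence is only a reason to check the rule.
- **The loss may be negligible.** At s = 5% the detectable effect is 0.300, still the planning value of 0.3, and the range for s has no source in the document. Both points stand. The top-up could also replace lost numbers, although it would not say whether a score of 10 qualifies.
- **The base of 7000 is a separate matter.** It does not depend on the inequality and adds no weight to it. It belongs here because any restatement of the yield has to use the right base.

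**Conclusion.** The inconsistency is real and should be corrected: Stage II entry is > 10 in the Hypotheses and ≥ 10 in the Sample size, and a score of exactly 10 falls between them. A slip in the Hypotheses is the likeliest explanation.

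The consequence concerns who is studied and how many. A single cut-off applied before individual randomisation affects both Stage II arms alike, so the comparison is not biased, and the Stage I primary hypothesis does not involve the threshold.

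On the chain as written, the detectable effect worsens by roughly 0.01 to 0.03, conditional on the assumed 5–20%. Those are not the trial's likely figures, because the chain counts both arms. With an equal split between arms, the detectable effect is about 0.41 even under ≥ 10, and 0.42–0.46 under > 10.

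**What to change.** Change the Hypotheses to PHQ-A ≥ 10 at 12 months, in line with the severity bands and the Sample size section, and confirm that the automated Stage II process applies that rule. The cost is one inequality sign and one check.

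If > 10 is what the investigators intend, keep the Hypotheses and restate the Stage II prevalence, yield and detectable effect for > 10.

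Under either choice, recompute the yield from intervention-arm students only. Settling on ≥ 10 removes the contradiction but does not rescue 525 and 368.

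As a minor wording point, the Sample size section also describes entrants as not having responded to the first app. It would be clearer to say that they still score at or above the chosen cut-off at 12 months.
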